### Statistical analysis plan

#### Sample size and power calculation (ANOVA)

To have an 80% chance of detecting as significant (at the 5% level) a ten point difference or more in mean total Constant score between the three groups, with an assumed standard deviation of 15 points and a loss to follow up of 10 patients in each group, a total of 162 patients is required.

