#### Data-analysis

No interim data-analysis will be carried out. The data-analysis will be conducted by a biostatician at the end of the follow-up period.

Patients randomised to the non-surgical management group but who cross-over and undergo secondary surgery will primarily be analysed as they were randomised. Similarly, patients randomised to osteosynthesis but due to surgical technical difficulties are treated with primary hemiarthroplasty, will be analysed as randomised.

Patients that drop-out after the six months evaluation will be included in the analysis based on six months data ('last observation carried forward'). Drop-out of patients before the six months evaluation cannot be included in the analysis.

Descriptive statistics (mean and standard deviations, as well as median and 10 and 90 percentiles for continuous variables, and frequency and 95 percent confidence interval for binary variables) will be calculated for each of the three groups, and their relevant subgroups, at both time points. Relevant subgroups include:

• Valgus-impacted versus classical four-part fractures

• Cross-overs from non-surgical treatment to secondary hemiarthroplasty versus non cross-overs in non-surgical treatment group

• Cross-overs from osteosynthesis to primary hemiarthroplasty versus non cross-overs in osteosynthesis group.

Continuous and binary baseline characteristics will be tabulated according to the three treatment groups. No statistical testing will be performed, but relevant imbalances will be noted and reported. Baseline characteristics include: age, ASA Score, patient's treatment preference, surgeon's treatment preference and fracture pattern (valgus-impacted or classical four-part).

The primary analyses of effect will be two analyses of variance (ANOVA) based on the overall Constant scores, and the Constant pain subscale score, measured at 12 months. We will use the last observation carried forward approach, excluding patients only because of missing data, and analyse all patients according to their randomisation (intention-to-treat analysis).

If one or both of the ANOVA analyses are statistically significant, we will subsequently perform a pair-wise testing based on t-tests:

• Osteosynthesis versus non-surgical management.

• Hemiarthroplasty versus non-surgical management.

• Osteosynthesis versus hemiarthroplasty.

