Thus, our protection against the risk of type 1 errors consists on a clear definition of the two primary outcomes and a single analysis ANOVA approach.

We will also conduct the following secondary analyses:

• The above analysis will be conducted for the following two subgroups: valgus-impacted and classical fractures respectively.

• In the osteosynthesis group we will conduct a subgroup analysis comparing patients with intraoperative change to hemiarthroplasty with those without.

• We will repeat the primary analysis as a mixed model for repeated measurements (including data from six months and the predefined covariates: age, ASA-Score, and treatment preference at baseline).

• The number of patients with Constant score ≥ 70 at month 12 for each group (and subgroup) will be compared with Chi-square tests.

The same analyses (except the third) will be performed for the other outcomes (Oxford Shoulder Score, Short Form-36).

Finally, we will perform a per protocol effect analysis in which only patients that were compliant with physiotherapy and training (attending > 75% physiotherapy sessions judged by physiotherapist) will be included.

The same analyses will be performed for the other outcomes (Oxford Shoulder Score, Short Form-36).

A three year follow-up analysis will be reported in a separate publication. The analyses will compare number of patients in each group that died, received shoulder surgery, etc.

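### The primary ANOVAs are valid but unadjusted, and no planned pooled estimate adjusts for fracture pattern: a missed efficiency of unknown size, not a bias

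*Protocol article*

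**What the plan says.** All references are to the protocol article.

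- **Primary analysis (Data-analysis).** "The primary analyses of effect will be two analyses of variance (ANOVA) based on the overall Constant scores, and the Constant pain subscale score", both at 12 months. If either is significant, "we will subsequently perform a pair-wise testing based on t-tests" for the three pairs of arms. Neither step names a covariate.
- **Baseline table (Data-analysis).** Age, ASA score, patient's and surgeon's treatment preference, and fracture pattern are tabulated by arm. On differences between arms: "No statistical testing will be performed, but relevant imbalances will be noted and reported".
- **Secondary analyses (end of the Data-analysis section).** The primary analysis is repeated as a repeated-measures mixed model that adds the six-month data and "the predefined covariates: age, ASA-Score, and treatment preference at baseline". Fracture pattern is not in that list. Pattern enters instead through separate analyses of valgus-impacted and classical fractures. The mixed model is the one analysis not carried over to the Oxford Shoulder Score and SF-36.
- **Aims.** The secondary aim is to study prognostic differences between the two patterns.
- **Blinding.** Pattern is classified from the baseline radiographs at the end of the study, before data analysis, by surgeons blinded to patient identity.
- **Sample size.** The calculation is labelled ANOVA and targets "a ten point difference or more in mean total Constant score between the three groups". It takes an SD of 15 and 10 losses per group, and arrives at 162 patients in all.

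**The concern.** The plan names baseline factors worth adjusting for, but adjusts for them only in a secondary model. The analysis that decides the trial uses none of them. Where such factors predict the 12-month Constant score, adjustment removes explained variance from the error term and corrects the estimate for whatever chance imbalance occurred. The unadjusted ANOVA does neither.

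Fracture pattern is the clearest gap. The protocol considers it important enough for a secondary aim. It is classified only at the end of the study, so that classification cannot have served to balance the arms at randomisation. Analyses within each pattern use smaller samples and do not yield a pattern-adjusted overall treatment effect.

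At stake is some power and precision on both primary outcomes. There is also the awkward position of a primary result and an adjusted secondary result that might disagree, with the adjusted one lacking the factor the protocol singles out.

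**Working it through.** **Inputs from the protocol.** 162 patients in three equal groups; 10 lost per group; SD 15; 10-point difference; 5% level; 80% power.

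**Assumed inputs.** The position of the middle mean is not stated; 0/5/10 is used. The share of outcome variance explained by the covariates (R²) is not given; 0 to 0.20 is shown.

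**Step 1: reproduce the plan's figure.**
- Analysed per group: 162/3 − 10 = 54 − 10 = 44.
- Sum of squared deviations of the means: (−5)² + 0² + 5² = 50.
- Noncentrality: λ = n × 50 / SD² = 44 × 50 / 225 = 9.78.
- Error degrees of freedom: 3 × 44 − 3 = 129.
- Noncentral F with 2 and 129 df at the 5% level: power 79.6%.

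This matches the stated 80% to rounding, and 3 × (44 + 10) = 162. Strictly reaching 80% needs 45 per group, or 3 × (45 + 10) = 165. The sample size and the unadjusted primary analysis therefore agree. With means 0/0/10 instead, 44 per group gives 90.2%, so 0/5/10 is the reading that recovers the plan's number.

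**Step 2: add covariates.** Residual variance becomes 225 × (1 − R²), so λ = 9.78/(1 − R²). Age, ASA score as a linear term and a two-level pattern use 3 df, leaving 126. The standard error (SE) of a pairwise difference is 15 × √(1 − R²) × √(2/44).

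| Assumed R² | λ | Power, 44 per arm | SE of a pairwise difference (points) |
|---|---|---|---|
| unadjusted | 9.78 | 79.6% | 3.20 |
| 0 | 9.78 | 79.6% | 3.20 |
| 0.02 | 9.98 | 80.5% | 3.17 |
| 0.05 | 10.29 | 81.7% | 3.12 |
| 0.10 | 10.86 | 83.9% | 3.03 |
| 0.20 | 12.22 | 88.1% | 2.86 |

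At R² = 0 the price of 3 df is 79.64% against 79.61%. Using 4 df (ASA groups 1–3 as categories) leaves every power figure unchanged at one decimal.

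**Step 3: how common is chance imbalance?** Simulating simple randomisation with 44 per arm, at least two arms differ by more than 0.25 SD on a standardised continuous covariate in about 47% of trials. For a binary factor with an assumed prevalence of 30% to 50%, a gap above 15 percentage points arises in about 28% to 35%. Such imbalance shifts the estimate only to the extent that the factor predicts outcome. The unadjusted standard error already allows for it on average over randomisations.

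**The case against.** An unadjusted ANOVA in a randomised trial is unbiased and controls type I error. The plan is coherent: it is sized by ANOVA, analysed by ANOVA, and relies on a single ANOVA approach as part of its type I error protection. An unadjusted primary analysis with a prespecified adjusted secondary one is a recognised choice. All of this stands, and it is why the point concerns efficiency only.

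The size of the gain is also unknown. The listed baseline characteristics include no baseline Constant score, and age, ASA score and a two-level pattern may explain little. This stands too, so the range has to include zero.

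Two stronger readings are tempting and not supported:

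- A reader might infer from the baseline-table sentence that chance imbalance is merely noted. It is not: the secondary mixed model adjusts for age, ASA score and preference, and pattern is examined in separate analyses. What remains is that the adjusted model is secondary and lacks pattern.
- A reader might infer that the trial already holds pattern to be prognostic. The aim is to study such differences, which leaves the question open. It is still reason enough to prespecify pattern as a covariate.

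A fair practical objection is that promoting the mixed model would also replace the last-observation-carried-forward rule and so change the handling of missing data. The fix below avoids this by using an ANCOVA.

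**Conclusion.** The point holds as a missed efficiency. The primary ANOVAs and t-tests use none of the baseline information the trial collects, and no pooled treatment estimate, primary or secondary, adjusts for fracture pattern. Nothing here makes the primary test invalid or the estimate biased, and 162 patients is consistent with the analysis as planned.

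The gain in power is nil at R² = 0, about 1 point at 0.02, 2 at 0.05, 4 at 0.10 and 9 at 0.20. These figures rest on means of 0/5/10, SD 15, 44 analysed per arm and an R² that the protocol does not supply. They refer to the Constant total score; no power is stated for the pain subscale. The case for the change is that the cost is negligible even when the covariates predict nothing.

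**What to change.** - Make both primary analyses (Constant total and pain subscale at 12 months) an ANCOVA with treatment arm, age, ASA score and fracture pattern. State in advance how age and ASA score are coded.
- Replace the pairwise t-tests, still conditional on the overall test, with adjusted contrasts from the same model.
- Keep the unadjusted ANOVA as a sensitivity analysis.
- Add fracture pattern to the covariates of the secondary mixed model, alongside age, ASA score and treatment preference.

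The analysis population and the last-observation-carried-forward rule can stay as written. No new data are needed: age and ASA score are already collected, and pattern is already to be classified from baseline radiographs before the analysis. The sample size need not change.

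The cost is three or four degrees of freedom and some rewriting of the primary analysis and pairwise-testing text. The gain may be small or absent if the covariates predict the Constant score poorly.

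### Nothing controls type 1 error across the two primary ANOVAs (about 7% to 10% rather than 5%), and the rule that opens the pairwise tests does not tie them to their own outcome

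*Protocol article*

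**What the plan says.** Under Outcome measures, the protocol article names two primary outcomes at 12 months: the Constant total score (0–100) and the Constant pain subscale (0–15). Under Data-analysis, the primary analyses are two ANOVAs, one for each outcome. The next step is: "If one or both of the ANOVA analyses are statistically significant, we will subsequently perform a pair-wise testing based on t-tests". Three comparisons are listed, covering every pair of the three arms, without any adjustment.

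The section then explains how error is controlled: the "protection against the risk of type 1 errors consists on a clear definition of the two primary outcomes and a single analysis ANOVA" approach.

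The only significance level in the document is in the sample size section, which aims for "an 80% chance of detecting as significant (at the 5% level) a ten point difference or more in mean total Constant score". That section does not mention the pain subscale.

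**The concern.** The document states what its type 1 error protection consists of, so this is not a detail left to a separate analysis plan. Two things in the statement do not deliver that protection.

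- **Across outcomes.** Naming two primary outcomes in advance prevents choosing among outcomes after seeing the data. It does not control the error from testing both and acting on either. The rule is that either outcome may succeed, not that both must.
- **Within an outcome.** An omnibus test protects three pairwise tests only if it is the omnibus test for that same outcome. The wording does not say which outcome's t-tests follow when only one ANOVA is significant.

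This rule decides when the trial may claim that osteosynthesis, hemiarthroplasty or non-surgical management differ, so it governs the main conclusion.

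**Working it through.** **Inputs from the protocol article.** Three groups of equal size; "a ten point difference or more in mean total Constant score between the three groups"; "with an assumed standard deviation of 15 points"; "a loss to follow up of 10 patients in each group, a total of 162 patients is required"; 5% level; 80% power. Evaluable patients per group: 162/3 − 10 = 44.

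**Assumptions not in the document.** The correlation between total and pain scores is not given, so 0 to 0.9 was examined. A positive value is expected because pain is a subscale of the total. The 5% level for the pain ANOVA is inferred, because no other level is stated. The simulations use bivariate normal outcomes.

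**1. Reproducing the plan's figure.** For a one-way ANOVA with means 0/5/10 and SD 15, the noncentrality is λ = n·Σ(mᵢ − m̄)²/SD² = n·(25 + 0 + 25)/225.

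- With n = 44, λ = 44 × 50/225 = 9.78, and power at 5% is 79.6%.
- Reaching a full 80% takes n = 45, so 3 × (45 + 10) = 165, within 3% of 162.

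The sample size thus reproduces for the total score alone, tested at an unadjusted 5%.

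**2. Error across the two ANOVAs when no treatment differs.** If independent, 1 − 0.95² = 0.0975. Simulation with 3 × 44 patients and 100,000 trials per setting gives:

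| Assumed correlation | P(at least one ANOVA significant) |
|---|---|
| 0 | 9.7% |
| 0.3 | 9.4% |
| 0.5 | 9.1% |
| 0.6 | 8.9% |
| 0.7 | 8.5% |
| 0.8 | 7.8% |
| 0.9 | 7.1% |

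In this setting the chance of at least one false pairwise claim is the same, whichever way the gate is read.

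**3. Error within one outcome.** If an outcome's t-tests are opened only by its own ANOVA, the error within that outcome is about 5.0%. This is expected with three groups. If all three means are equal, the ANOVA holds 5%. If one arm differs, only one true null comparison remains, and it is tested at 5%.

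**4. Error if either ANOVA opens t-tests on both outcomes.**

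- Total differs by 0/5/10 points (SD 15), pain null: a false pairwise claim on pain in 10.4% to 10.7% of trials, over correlations 0 to 0.8.
- Total differs by a large amount, pain null: 12.2% to 12.3%.
- Pain differs by 1 SD in one arm, total null: a false pairwise claim on the total in 12.2%.

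With a large effect on one outcome the gate is always open, so the other outcome faces three unadjusted t-tests. That makes about 12% an upper bound.

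**5. What correction would cost.** Testing the total at 2.5% lowers power at 44 per group from 79.6% to 70.6%. Restoring 80% would take 53 per group, or 3 × (53 + 10) = 189 patients. A fixed sequence starting with the total keeps 5% for that test, and so keeps 79.6% and 162.

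**The case against.** **The stated protection is partly real.** A reader might infer that there is no protection at all. That goes too far: step 3 shows that an ANOVA gate holds about 5% within an outcome when it is that outcome's own gate. This part of the objection stands.

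**No 5% family-wise rate is promised.** A reader might also infer that the error is nearly twice a rate the protocol commits to. The document gives 5% only in the power calculation for the total score. The top figure of 9.75% needs independence, which is unlikely for a scale and its own subscale; at a correlation of 0.9 the error is about 7%. This stands too, so the size must be given as a range.

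**The phrase about a single ANOVA may be loose rather than false.** The same sentence mentions two primary outcomes, so the authors knew there were two ANOVAs. They may have meant one omnibus test per outcome in place of three pairwise tests. Even on that reading, nothing covers the two outcomes together.

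**The cross-opening of t-tests is one reading, not an established rule.** An ordinary reader may take the t-tests to follow whichever ANOVA was significant. The 12% figure needs the literal reading and a strong effect on one outcome with none on the other. A pain effect with an exactly null total is unlikely, since pain points count towards the total. A total effect with null pain is easier to imagine, but at the design effect it gives 10% to 11%, not 12%.

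**Powering on the total alone is not an error.** Agreed; the figure reproduces.

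**Conclusion.** The error-control statement is wrong as written. The plan runs two primary ANOVAs, lets either one lead to claims, and has nothing that controls error across them. The chance of at least one false-positive primary ANOVA when no treatment differs is about 7% to 10%, depending on the assumed correlation and on 5% being the level for pain. It stays above 5% at every correlation examined, from 0 to 0.9.

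Within one outcome the ANOVA gate can hold about 5%, but the text leaves open whether each outcome has its own gate. The documents do not settle that ambiguity, so about 12% is an upper bound under one reading in a stylised case, not the expected error of the trial. Recruitment, allocation and the sample size calculation are not affected.

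**What to change.** Before unblinding, replace the error-control sentence under Data-analysis with a named procedure that covers both primary outcomes. The choice is the sponsor's. Two that work:

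- **Fixed sequence.** Test the Constant total at 12 months at 5%; test pain at 5% only if the total is significant. This keeps 162 patients and 79.6% power for the total. The downside is that pain cannot be confirmatory if the total is null.
- **Holm or Hochberg across the two ANOVAs.** Pain can then succeed alone. Power for the total may fall from 79.6% to as low as 70.6%, when it has to be tested at 2.5%.

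In either case, run the pairwise t-tests for an outcome only if that outcome's own ANOVA is significant under the procedure. Delete the wording that lets one or both ANOVAs open the pairwise tests, and delete the claim of a single ANOVA. With the fixed sequence this is a change of wording only.

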### Aims

Our primary aim is to compare the effect of osteosynthesis with angle-stable plate with non-surgical management for displaced four-part fractures in elderly. We also aim to compare the effect of primary hemiarthroplasty with both osteosynthesis and with non-surgical management.

Our secondary aim is to study prognostic differences between two pathoanatomical patterns of displaced four-part fractures: 'valgus impacted' four-part fractures and 'classical' four-part fractures (Fig. 1) [18].

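### The secondary aim is to compare prognosis between the two fracture patterns, but the tests planned by pattern compare treatments within each pattern and no between-pattern contrast is stated

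*Protocol article*

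**What the plan says.** Under Aims, the protocol article states: "Our secondary aim is to study prognostic differences between two pathoanatomical patterns of displaced four-part fractures". The two patterns are valgus-impacted and classical.

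Under Data-analysis, pattern or subgroup enters in three places:

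- **Descriptive statistics.** These "will be calculated for each of the three groups, and their relevant subgroups, at both time points", and the first subgroup listed is "Valgus-impacted versus classical four-part fractures".
- **First secondary analysis.** "The above analysis will be conducted for the following two subgroups: valgus-impacted and classical fractures respectively". The analysis referred to is the primary one: "The primary analyses of effect will be two analyses of variance (ANOVA) based on the overall Constant scores" and the pain subscale, followed by pairwise t-tests between treatments if an ANOVA is significant.
- **Fourth secondary analysis.** The numbers reaching a Constant score of at least 70 "for each group (and subgroup) will be compared with Chi-square tests".

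The mixed model in the third secondary analysis uses the "predefined covariates: age, ASA-Score, and treatment preference at baseline". Fracture pattern is not among them, although the same section lists it as a baseline characteristic.

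**The concern.** A prognostic difference between patterns is a difference in outcome between patients with one pattern and patients with the other. A difference in treatment effect between patterns is an interaction. An ANOVA of treatment arms run inside one pattern estimates neither.

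Two things are at stake. First, the trial may end without a formal answer to its declared secondary aim, although its data could give a fairly precise one. Second, two underpowered ANOVAs printed side by side tempt readers to conclude that treatment works in one pattern and not in the other, when the difference in significance is only chance.

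**Working it through.** **Inputs.** From the sample size section: 5% level, 80% power, 10-point difference in Constant score, SD 15, 162 patients, 10 lost per group. With three equal groups that is 54 per arm, 44 evaluable per arm and 132 evaluable in total. The share of valgus-impacted fractures is not given, so I assume 50%, 40%, 30% and 20%, equal across arms.

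**1. The plan's own figure.** For a one-way three-arm ANOVA with means 0/5/10, the noncentrality is λ = n × Σ(mean − grand mean)² / SD² = n × 50/225. With n = 44, λ = 9.78 and power is 0.796, which matches the stated 80%. The smallest n per arm reaching 0.80 is 45, giving 3 × (45 + 10) = 165, within 3 patients of 162. Means 0/0/10 need only 34 per arm, or 3 × (34 + 10) = 132, and do not match. I therefore use 0/5/10 below.

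**2. What a within-pattern ANOVA says about prognosis.** Adding a constant to every score in one pattern changes neither the between-arm nor the within-arm sum of squares in that pattern, so F is unchanged. A simulation agrees. With 22 per arm per pattern, no treatment effect and a true shift between patterns of 0, 10 or 20 points, each within-pattern rejection rate stayed between 0.046 and 0.052.

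**3. Reading the two results against each other.** Take the same 0/5/10 effect in both patterns. Let p₁ and p₂ be the within-pattern powers, from the formula in step 1. Then P(exactly one significant) = p₁(1 − p₂) + p₂(1 − p₁). At 50:50, n = 22 per arm, λ = 4.89, power is 0.475, and 2 × 0.475 × 0.525 = 0.50.

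**4. Direct between-pattern contrast, adjusted for arm.** For a 10-point difference, λ = 10² / [225 × (1/N₁ + 1/N₂)] with 1 and 128 df. At 50:50 (66 v 66), λ = 14.67. At 20:80 (26.4 v 105.6), λ = 9.39. The difference detectable with 80% power is (1.96 + 0.84) × 15 × √(1/N₁ + 1/N₂).

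**5. Treatment-by-pattern interaction.** With the full 0/5/10 effect in one pattern and none in the other, λ = 50 / [225 × (1/n₁ + 1/n₂)] with 2 and 126 df, where n₁ and n₂ are patients per arm in each pattern. At 50:50, λ = 2.44. At 20:80, λ = 1.56.

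| Split | Within-pattern power | Exactly one significant | Direct contrast, 10 points | Detectable at 80% | Interaction power |
|---|---|---|---|---|---|
| 50:50 | 0.475 / 0.475 | 0.50 | 0.97 | 7.3 | 0.26 |
| 40:60 | 0.39 / 0.56 | 0.51 | 0.96 | 7.5 | 0.25 |
| 30:70 | 0.29 / 0.63 | 0.55 | 0.94 | 8.0 | 0.23 |
| 20:80 | 0.20 / 0.69 | 0.62 | 0.86 | 9.1 | 0.18 |

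**The case against.** The aim is worded as studying differences, with no hypothesis or threshold, so description is a defensible if thin answer. The descriptive plan does give means, SDs and percentiles for each pattern within each arm, and a difference can be read from them. The Chi-square item could mean that patterns are compared with each other. The within-pattern ANOVAs can be taken simply as asking about treatment effect in each pattern. The article is also a condensed document, and the full plan may state the contrast.

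Much of this stands, and it limits the point. A reader might infer that the plan offers no estimate at all relevant to its secondary aim. The descriptive plan shows otherwise; what is missing is a stated between-pattern difference with its uncertainty. A reader might also infer that the authors intend to claim effect modification from one significant and one non-significant ANOVA. The article states no such rule, so the 50–62% measures a risk of misreading and is not a planned error rate.

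Two parts of the defence do not carry. The Chi-square wording is ambiguous, and on its most favourable reading it compares only a dichotomised score. Condensation does not explain the gap either: the article fixes a specific method for the patterns, and that method does not match the aim. The next item on the list does state a direct comparison, between patients converted during osteosynthesis and those not converted.

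**Conclusion.** The point holds in a limited form. The stated aim concerns differences between patterns, and the inferential analysis clearly assigned to pattern concerns differences between treatments. No between-pattern Constant difference with a confidence interval and no interaction is stated. Followed as written, the plan leaves its secondary aim with descriptive tables only.

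The algebra in step 2 depends on no assumption about the pattern split. The sizes are conditional. The chance of 50% to 62% that exactly one pattern is significant assumes an identical 0/5/10 effect in both patterns, SD 15, 132 analysed, splits from 50:50 to 20:80, and a reader who sets the two results against each other. The power of 97% to 86% for the direct contrast borrows 10 points from the treatment comparison, because the article sets no prognostic difference.

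The sample size and the primary analyses are not affected. This is a correction that should be made to a secondary analysis, not a threat to the trial's main conclusion.

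**What to change.** 1. **Answer the secondary aim directly.** Fit one model to the 12-month Constant score on all analysed patients, with treatment arm and fracture pattern and without their interaction. Report the difference between patterns with a 95% CI. The interaction is left out here because, once it is in the model, the pattern main effect depends on how the factors are coded and is no longer a single answer.
2. **Add the treatment-by-pattern interaction as a separate analysis, labelled exploratory.** State that its power is about 18–26% even when the full effect exists in only one pattern, so a non-significant result is not evidence of equal effects.
3. **Report within-pattern treatment effects as estimates with CIs**, in place of separate significance tests.
4. **Reword the Chi-square item** to say whether treatments are compared within each pattern or patterns are compared with each other.

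No new data are needed: the Blinding section already has pattern classified from baseline radiographs before the data analysis. The cost is a change of wording and one extra model. The downside is small: an interaction test that is unlikely to be conclusive.
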